## Abstract

**Background:**

Chronic prostatitis/chronic pelvic pain syndrome is a highly prevalent syndrome. Previous studies showed that extracorporeal shockwave therapy and myofascial release therapy could improve the quality of life in patients with chronic prostatitis/chronic pelvic pain syndrome (CP/CPPS). Theoretically, combined therapy with extracorporeal shockwave therapy and myofascial release therapy will likely have significant advantages in treating CP/CPPS. We, therefore, present a protocol for conducting a well-designed randomized controlled trial to compare the efficacy and safety of each therapy.

**Methods:**

The proposed study will be a three-group randomized control trial (RCT) design that includes 150 participants from Zhongda Hospital Affiliated to Southeast University, with equal allocation of participants to the three intervention groups. The study duration will be 8 weeks, which includes a 4-week treatment period and a 4-week follow-up period. The primary outcome will be the changes in surface electromyography (sEMG) assessment and National Institutes of Health-Chronic Prostatitis Symptom Index (NIH-CPSI). The secondary outcomes will include the changes in three-dimensional quantification, shear wave elastography (SWE), and sympathetic skin response (SSR) testing. Assessments will be conducted before the intervention (T0), before the 5th intervention (T1), immediately after the 8th intervention (T2), and the 4th week after the end of the 8th intervention (T3).

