#### Pre-resting sEMG

Patients will be required to rest for 1 min to relax the abdominal, gluteal, and perianal muscles fully. Then, we will measure the amplitude and coefficient of variation of pelvic floor muscle resting tone (coefficient of variation = standard deviation/mean). Mean sEMG values greater than 4 μV suggest that the pelvic floor muscle tone is elevated and the muscle is in a state of spasm, which may result in ischemia and hypoxia in the muscle tissue and cause pelvic tissue pain. If the resting coefficient of variation is greater than 0.2, subject to unconscious contractions, suggesting a decrease in PFM stability. It causes symptoms such as painful intercourse, premature ejaculation, and constipation. Tight pelvic floor muscle groups with string-like tight bands and painful trigger points can be felt during palpation.

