#### Tense contraction phase sEMG

Patients will be required to relax for 10 s and then contract for 10 s and repeat 5 times. The amplitude of the systolic wave and coefficient of variation of the slow muscle, mainly to test slow dynamic muscle strength and stability of contractile control, were assessed, with a mean sEMG of values greater than 35 μV and a coefficient of variation less than 0.2 in the normal state. When muscle strength decreases, and a coefficient of variation exceeds 0.2, symptoms such as premature ejaculation, erectile dysfunction, and urinary frequency are prone to be present.

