#### Endurance contraction phase sEMG

Patients will be required to relax for 10 s and then perform an endurance contraction lasting 60 s. It aims to assess the endurance of slow muscle fiber, to test the pelvic floor muscle sEMG, especially the slow muscle fiber (normal: mean sEMG values greater than 30 μV, coefficient of variation less than 0.2). A decrease in the mean value of this stage indicates a decrease in the endurance of slow muscle fiber.

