### Sample size calculation

Previous studies showed that myofascial release therapy had notable effects [32] (corresponding to a Cohen’s *d* of about 0.5) on improving quality of life, prostate-related symptoms, and pain. The primary outcome will be the change in NIH-CPSI scores, the clinical response rate, and the remission rate as measured by the NIH-CPSI 4 weeks after the completed intervention. We assumed that extracorporeal shockwave combined with myofascial release therapy had similar effects on NIH-CPSI scores. A sample of 40 participants per group was computed by the G*power software to achieve a power of 60% and a level of significance of 5% and a 95% confidence level. To compensate for an estimated dropout rate of 25%, 150 participants will be ultimately required. (i.e., the number in each group is 50).

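### The primary outcome is defined in two incompatible ways, and the sEMG part does not say which of its eight measures counts

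*Protocol article*

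**What the plan says.** The protocol article defines the primary outcome twice.

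- **Abstract, Methods:** "The primary outcome will be the changes in surface electromyography (sEMG) assessment and National Institutes of Health-Chronic Prostatitis Symptom Index (NIH-CPSI". The Primary outcome measures section lists the same two instruments. Study design and Plans for assessment and collection of outcomes schedule the primary measurements at T0, T1, T2 and T3, without saying which visit is decisive.
- **Sample size calculation:** the primary outcome is "the change in NIH-CPSI scores, the clinical response rate, and the remission rate as measured by the NIH-CPSI 4 weeks after the completed intervention". Four weeks after treatment is T3. sEMG is not mentioned.

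The sEMG assessment has four phases. Before exercise, at rest, the investigators will "measure the amplitude and coefficient of variation of pelvic floor muscle resting tone"; a mean above 4 μV is taken to "suggest that the pelvic floor muscle tone is elevated and the muscle is in a state of spasm". In tense contraction the measures are "The amplitude of the systolic wave and coefficient of variation of the slow muscle", "with a mean sEMG of values greater than 35 μV and a coefficient of variation less than 0.2 in the normal state". In endurance contraction a mean above 30 μV with a coefficient of variation below 0.2 is normal, and "A decrease in the mean value of this stage indicates a decrease in the endurance of slow muscle fiber". At rest after exercise, amplitude and coefficient of variation are measured again, and above 4 μV is again elevated.

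Statistical methods sets p < 0.05 for significance. It plans a repeated-measures ANOVA of sEMG and NIH-CPSI over T0 to T2, and triggers post hoc tests when any outcome variable shows a significant difference. The next sentence says a Bonferroni correction will adjust the alpha levels, without giving a family or a number of tests.

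**The concern.** A confirmatory trial needs one fixed answer to the question of what result counts as success. Here three parts of that answer are open: which instruments are primary, which sEMG measure represents sEMG, and at which visit. If the choice is made after the data are seen, a chance finding on one measure can be reported as the primary result, and the nominal 5% no longer describes the risk of a false claim.

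The sEMG part has a further ambiguity. A treatment that lowered amplitude in every phase would look better at rest and worse in contraction. A change in sEMG, taken as a whole, therefore does not define benefit.

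**Working it through.** **1. The two definitions side by side**

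| | Abstract and Primary outcome measures | Sample size calculation |
|---|---|---|
| NIH-CPSI change | yes | yes |
| sEMG | yes, measure not named | absent |
| Response and remission rates | not named as primary | yes |
| Time point | not fixed (T0 to T3) | T3 |

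The NIH-CPSI text gives four categories by percentage fall in score, but does not say which of them is response and which is remission.

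**2. Counting the sEMG measures.** Four phases × 2 (amplitude or mean, and coefficient of variation) = 8. This is a tally from the four phase descriptions; the protocol does not state the number. For amplitude, lower is better in the two resting phases and higher is better in the two contraction phases. With NIH-CPSI, the first definition holds 8 + 1 = 9 measures. The second holds 3.

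**3. Reproducing the plan's sample size.** Inputs from Sample size calculation: d = 0.5, alpha 5%, power 60%. Two-sided testing is assumed because sidedness is not stated.

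n per group = 2(1.960 + 0.253)² / 0.5² = 2 × 4.90 / 0.25 = 39.2, rounded up to 40.

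Power at n = 40 is Φ(0.5 × √20 − 1.960) = Φ(0.276) = 61%; the exact t-test gives 59.8%. One-sided testing would give 29, so it does not match. The stated 40 is therefore one two-sided comparison of two groups on one outcome, with no allowance for further outcomes.

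**4. Chance of at least one false positive if any one measure may count at 0.05.** Under independence this is 1 − 0.95^k.

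- k = 9: 1 − 0.95⁹ = 37.0%
- k = 3: 1 − 0.95³ = 14.3%

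The protocol gives no correlations, so a range is assumed. Simulating nine equally correlated outcomes, each with a three-group F test (40 per group, 20,000 runs), gives:

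| Assumed correlation | At least one false positive |
|---|---|
| 0.3 | 32.8% |
| 0.5 | 28.2% |
| 0.7 | 21.2% |
| 0.9 | 12.5% |

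These figures count one overall test per measure; testing several time points would raise them. For k = 3, 14.3% is a ceiling, because all three outcomes come from the same NIH-CPSI score and are strongly related.

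**5. What keeping all nine would cost.** Bonferroni alpha is 0.05/9 = 0.0056. Power at 40 per group and d = 0.5 falls from 61% to about 30%. Restoring 60% needs about 74 per group before dropout.

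**6. What two co-primaries would cost,** assuming d = 0.5 for sEMG as well. If both are required, power lies between 0.61 × 0.61 = 37% (independent) and 61% (perfectly correlated). If alpha is split at 0.025 each, power for each outcome is Φ(2.236 − 2.241), about 50%.

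**7. Does the planned analysis reach T3?** The between-group ANOVA stops at T2. T3 enters only through a paired t-test of T2 and T3, so the T3 primary in Sample size calculation has no suitable between-group analysis.

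**The case against.** Several points on the other side have force.

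- **The Bonferroni sentence carries no explicit limit.** That it covers only post hoc comparisons is an inference from its position. A reader might conclude that the error rate is certainly above 5%; the text does not support that certainty. It supports only that coverage of the primary outcomes is unclear. An analysis plan that is not shown may define the family. It could not remove the contradiction between two current sections without overriding one of them.
- **The abstract joins sEMG and NIH-CPSI with an and.** If both must succeed, pairing them adds no type I error and costs power instead. No such rule is stated, and the choice among eight sEMG measures would remain.
- **A reader might add the two definitions together** and quote 11 measures with a 43% error rate (1 − 0.95¹¹). That total mixes two incompatible definitions and matches neither. The figures for nine and for three are the ones that correspond to something the protocol says.
- **The differing directions of amplitude are not an error.** The reference values for amplitude are clear phase by phase, and direction does not change the error rate. It matters only because no single measure is named.
- **sEMG is primary for a reason.** The Discussion faults earlier trials for relying on a subjective scale, so demoting sEMG is a real loss to the trial's rationale.

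These points narrow the claim about error control and widen the acceptable remedies. They leave untouched the conflicting definitions and the unnamed sEMG measure.

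**Conclusion.** The point holds and should be corrected before analysis. The protocol gives two primary outcomes that cannot both be right, names none of eight sEMG measures as the one that counts, states no success rule, and does not clearly control error across outcomes.

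The size is conditional. If success on any one of nine measures at p < 0.05 were enough, the false-positive risk would run from 37% under independence down to about 12% at a correlation of 0.9, above 5% throughout. Under the sample-size definition it is at most about 14%, and less in practice. Both figures rest on an either-is-enough rule and on Bonferroni not applying across outcomes; the first also rests on assumed equal correlations. The protocol neither states nor rules out these conditions. The sample size supports one outcome only.

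**What to change.** 1. Name one primary variable and time point: NIH-CPSI total score at T3, adjusted for T0. It already appears in the sample-size section, and the 40 per group fits it.
2. Make pre-resting mean sEMG amplitude the first key secondary, tested only if the primary is significant. Elevated resting tone is the mechanism the protocol sets out to examine. If the sponsor wants an objective primary, keep this single measure as a co-primary, state whether both are required or alpha is split, and restate the power.
3. Label the other seven sEMG measures and the response and remission rates as supportive.
4. Align the abstract, Study design, Primary outcome measures, Plans for assessment and collection of outcomes, and Sample size calculation.
5. Amend Statistical methods so that the between-group analysis includes T3, and state which family of tests the Bonferroni correction covers.

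The cost is a substantive amendment to the protocol and registry while recruitment is under way, completed before any unblinded analysis. No added participants are needed for a single primary at the stated 60% power. sEMG loses full primary status or, if kept as a co-primary, costs power.

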**Discussion:**

This trial will compare the differences in efficacy between single extracorporeal shockwave therapy, single myofascial release therapy, and combined therapy to select the most appropriate treatment option for patients with CP/CPPS. The possible pathogenesis of CP/CPPS would also be analyzed by comparing the intercorrelation between each objective and subjective measurement (NIH-CPSI score, sEMG, SWE, SSR).

**Trial registration:**

The name of the registry: Extracorporeal Shockwave and Myofascial Release Therapy in Chronic Pelvic Pain Syndrome.

Registration number: NCT05659199. Date of registration: December 2022.

**Supplementary Information:**

The online version contains supplementary material available at 10.1186/s13063-023-07633-1.

## Background

Chronic prostatitis/chronic pelvic pain syndrome (CP/CPPS) is a kind of psycho-neuromuscular disorder [1, 2]; the global prevalence of CP/CPPS is between 9 and 16% [3]. In China, the prevalence of chronic prostatitis/chronic pelvic pain syndrome is about 3.9% [4]. Predisposing factors for CP/CPPS include sedentary behavior, excessive masturbation, frequent sexual intercourse, high psychological stress, anxiety, and depression [5]. With the increase in sedentary behavior during the COVID-19 pandemic, the prevalence is likely to be underestimated [6]. Chronic non-cyclical pelvic pain and discomfort in the pelvic region caused by CP/CPPS usually lasts for at least 3 of the past 6 months [7] and is often accompanied by lower urinary tract symptoms [8], psychosocial impairments, sexual dysfunction, postejaculatory pain [9], and pelvic floor muscle (PFM) pathology change [10]. The specific symptoms are pain in the groin and penile root, pain during erection, frequent urination, and a burning sensation in the urethra [11, 12]. It is now well-accepted that pelvic region pain can impair patients’ psychological state and quality of life [13]. Epidemiological studies have shown that psychosocial changes such as anxious depressive states and stress reactions [14] caused by CP/CPPS can further exacerbate pain symptoms severely [15]. Also, somatization symptoms, depression, anxiety, and pain catastrophizing were associated with physical HRQoL 12 months after treatment [16]. For this reason, it is vital to develop effective interventions to alleviate pain caused by CP/CPPS.

One of the causes of pelvic pain may be the spasm of PFM and impaired ability to relax [17]. When palpating the pelvic floor muscles of the patients, there are apparent tender points. The tissue at the tender point differs from the surrounding muscle tissue, with a certain degree of sliding limitation and ischemic sclerosis. Myofascial release therapy can potentially reduce muscle stress, create flexible fascial structures, and improve vascularization and innervation of the affected region [18]. The fascia trigger point is less painful, and tissues are softer after myofascial release therapy. However, patients may experience physical and psychological discomfort because the treatment will pass through the rectum. Palpation by the rehabilitation therapist is one of the most common procedures used to determine the muscle state of pelvic floor. However, this method is too subjective. So, we will evaluate pelvic floor muscle surface electromyography to determine if CP/CPPS patients commonly have elevated pelvic floor muscle tone at rest.

The existing body of clinical research on CP/CPPS suggests that extracorporeal shockwave effectively reduces pain and urinary tract discomfort and improves patients’ quality of life, with good long-term outcomes [5, 19–21]. To explain this result, Hung-Jen Wang [22] proposed the sequence of central pain processing, and the nociceptive effect at DRG was retrogradely attenuated, followed by the decrease of COX-2 and NGF expression in the prostate after Li-ESWT, which then provides long-term pain relief. However, they have rarely explained the role of extracorporeal shockwaves in changing pelvic floor muscle tone and elasticity. On the other hand, we found the fact that some reports on cardiovascular research show extracorporeal shockwave can effectively relieve muscle spasm in patients with hemiplegia [23–25], which may help relieve the increased pelvic floor muscle tone in patients with chronic pelvic pain syndrome [25–27].

Previous studies reported that abnormal autonomic nervous system (ANS) might correlate with chronic pelvic pain [28]. However, to date, few objective assessment indicators have been used for evaluating autonomic nervous function in patients with CP/CPPS. This study employs, for the first time, evaluation of sympathetic skin response. The main reason for choosing this measurement is that SSR can reflect the functional state of the postganglionic fibers of the sympathetic design, although its effectiveness in evaluating CP/CPPS patients has not been systematically investigated.

The primary aims of this research are threefold: (1) to identify more relatively effective interventions for improving pain symptoms in CP/CPPS patients; (2) to ascertain the correlation between PFM elastic modulus and tenderness symptoms; this study may find a more objective method of assessing efficacy; and (3) to determine the correlation between the intensity of the sympathetic skin response and the patient’s symptoms and to explore other possible pathogenetic mechanisms.

### Composition of the coordinating center and trial steering committee

The coordinating center comprises clinicians and therapists from the Department of Rehabilitation and the Department of Ultrasonography of Zhongda Hospital. The principal therapists will supervise this trial and be responsible for the medical responsibility of patients. There is no trial steering committee (TSC) for this trial.

### Study setting

This trial (NCT05659199—ClinicalTrials.gov) is a monocenter randomized controlled trial with three groups conducted in Department of Rehabilitation and the Department of Ultrasonography of Zhongda Hospital, Nanjing, Jiangsu, China. Zhongda Hospital is a teaching hospital, where the total number of outpatients annually is 2.03 million. The Zhongda Hospital has a dedicated Pelvic Floor Health Management Centre to assess, treat, and follow-up patients with pelvic floor dysfunction. Patients admitted to the Pelvic Floor Health Management Center include those seeking postpartum pelvic floor rehabilitation, those with chronic pelvic pain syndrome, and others with pelvic floor dysfunction. Treatment provided by the Pelvic Floor Health Management Center includes pelvic floor biofeedback electrostimulation, pelvic floor magnetic stimulation, extracorporeal shockwave therapy, and myofascial release therapy. Myofascial release therapy is a kind of manipulation therapy. Between 2020 and 2023, more than 1000 patients with pelvic floor dysfunction were treated at the Pelvic Floor Health Management Center. In this trial, the subjects included will be randomly assigned to the extracorporeal shockwave, myofascial release, and combined therapy groups.

### Composition of the data monitoring committee

IEC (Independent Ethics Committee) for Clinical Research of Zhongda Hospital, which is independent of the sponsor and competing interests, will be responsible for monitoring the data of the trial.

### Objectives

Thus far, there is a lack of well-designed randomized controlled trials to compare the efficacy of the two treatments, as well as a unified objective evaluation index. Furthermore, these assessment procedures (mainly based on palpatory findings) typically suffer from issues of reliability and validity, although there has been a recent increase in the literature on this topic. The intervention protocols were seldom standardized and more frequently semi-standardized. The overall quality of evidence was judged as “very low.” All the RCTs did not follow the blinding procedures, certainly for participants and personnel.

## Methods and analysis

### Study design

The proposed study will be a three-group randomized control trial (RCT) design that includes 150 participants from Zhongda Hospital Affiliated to Southeast University, with equal allocation of participants to the three intervention groups. The research flow chart is shown in Fig. 1. The reporting of this protocol is strictly based on the Standard Protocol Items: Recommendations for Interventional Trials (SPIRIT), which is found in Additional file 1.

**Fig. 1 Fig1:**
[figure not shown]
Research flowchart

General information, medical/treatment history, and pre-assessment results of each participant will be confidentially collected by the research assistant before the initial intervention.

Assessments will be conducted before the intervention (T0), before the 5th intervention (T1), immediately after the 8th intervention (T2), and at the 4th week after the end of the 8th intervention (T3), which include the surface EMG evaluation of pelvic floor muscles, NIH Chronic Prostatitis Symptom Index (NIH-CPSI), three-dimensional quantification, shear wave elastography, and the sympathetic skin response.

The primary outcome measurements will be performed at T0, T1, T2, and T3. Secondary outcome measurements will be carried out at T0 and T3.

The SPIRIT figure is displayed in Table 1.

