### Eligibility criteria

Patients with hormone abnormalities are excluded because thyroid dysfunction and testosterone may affect prostate function and myofascial status.

Participants will be screened using the following criteria.

Inclusion criteria:According to the National Institutes of Health classification of prostatitis [29], all male patients meet the diagnostic criteria for chronic prostatitis type IIIB/chronic pelvic pain syndrome (pain in the bladder, groin, perineal area, genitalia or lower abdomen with no significant abnormalities on urological examination);Patients are aged 20–40 years;Patients with chronic pelvic pain lasting over 6 months;Patients sign the informed consent form.

Exclusion criteria:Patients with significant coagulation disorders, perineal anatomical abnormalities, hormonal abnormalities, and neurological abnormalities;Patients with an apparent cause of pelvic pain, such as a history of previous surgery, chronic infection, trauma, prostatitis, and epididymitis;Patients receiving other treatments during the study;Patients with any urethral pathology;Patients who have had closed lumbar injections and previous lumbar surgery within 6 months;Patients with other conditions causing pelvic pain;Patients with contraindications to physiotherapy;BMI > 22.9

Termination and shedding criteria:Other serious illnesses occur in the course of treatment;Poor patient adherence and failure to complete the full course of treatment.

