### Criteria for discontinuing or modifying allocated interventions

Patients receiving other treatments during the study will be excluded as exclusion criteria, but rehabilitation interventions will still be provided. Participants who experienced severe adverse events during the intervention will discontinue treatment, and the data that have been collected will be used for subsequent data analyses.

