### Strategies to improve adherence to interventions

Three groups of participants will be treated by specially trained therapists and the intervention process will strictly follow the study protocol. If the participant is not treated and evaluated at the specified time interval, the primary investigator will contact the participant to ensure that the intervention is proceeding rigorously. If the participant continues to be absent from the treatment as needed or firmly withdraws from the study, the relevant data that have been collected will be used for subsequent data analyses.

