#### Intervention C—combined therapy group

In addition to routine palpation, the combined intervention group will be treated with extracorporeal shockwave and myofascial release therapy in a format identical to that of interventions A and B.

All the treatment will be administered once a day, 2 times a week, at no less than 2-day intervals for 4 weeks, for a total of 8 sessions.

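### As written, a patient who stops before the 8th session has no scheduled T2 or T3, so the sized endpoint is compared among completers only

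*Protocol article*

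**What the plan says.** The abstract and the study design text (under Fig. 1) define every post-baseline assessment by session number. T1 comes before the 5th session, and the last two come "immediately after the 8th intervention (T2), and at the 4th week after the end of the 8th intervention (T3"). The intervention section plans twice-weekly treatment "for a total of 8 sessions". The abstract gives the nominal calendar for the 8-week study, "which includes a 4-week treatment period and a 4-week follow-up period".

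The sample size section sets the sized outcome "as measured by the NIH-CPSI 4 weeks after the completed intervention".

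Three sections deal with patients who do not finish:

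- Eligibility criteria, termination and shedding: "Poor patient adherence and failure to complete the full course of treatment".
- Criteria for discontinuing interventions: patients with severe adverse events "will discontinue treatment, and the data that have been collected will be used for subsequent data analyses".
- Strategies to improve adherence: one rule covers a participant who "continues to be absent from the treatment as needed or firmly withdraws from the study, the relevant data that have been collected" are then used for analysis.

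The retention section adds a telephone call two weeks after the last intervention, in support of the visit at four weeks.

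**The concern.** The anchor for T2 and T3 is an event that an early stopper never reaches. None of the text on stopping supplies another date, and the adherence section handles absence from treatment in the same way as leaving the study. A man who no longer attends sessions may still be willing to fill in a symptom questionnaire, but the plan gives no occasion to ask him.

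Completing eight sessions happens after randomisation and may depend on the assigned treatment. The harm section expects perianal pain in about 15% with transrectal release and a very low probability of side effects with shockwave. The background says the rectal route may cause physical and psychological discomfort. If completion differs between arms in rate or in kind, a contrast among completers no longer compares the groups as randomised. The main analyses do not repair this: the repeated-measures ANOVA runs over T0 to T2 and the paired test uses T2 and T3, both of which an early stopper lacks. A separate analysis plan could not recover an outcome that was never collected.

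**Working it through.** **1. What the schedule yields, by point of stopping.**

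| Last session received | Assessments that acquire a date |
|---|---|
| 3 | T0 |
| 5 | T0, T1 |
| 8 | T0, T1, T2, T3 |

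The sized endpoint is NIH-CPSI at T3, so only the last row contributes to it. The discontinuation and adherence sections keep what the first two rows hold and schedule nothing further. The termination criterion points the same way, since an incomplete course itself ends participation.

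**2. The plan's own sample size.** Inputs from the sample size section: d = 0.5, power 60%, significance level 5% (two-sided assumed, as sidedness is not stated).

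n per arm = 2(z₀.₉₇₅ + z₀.₆₀)²/d² = 2(1.960 + 0.253)²/0.25 = 39.2, rounded up to 40. This reproduces the stated 40. Then 40 × 1.25 = 50 per arm and 3 × 50 = 150, as stated.

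**3. How many T3 values are at risk.** 25% of 50 is 12.5, so about 12 to 13 per arm could lack T3, leaving 37 to 38. This is an upper bound for the present point: the plan does not split the 25% into patients who only stop treatment and patients who refuse all contact.

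Pairwise power is Φ(d√(n/2) − 1.96). At n = 50 it is 70.5%; at n = 37 and 38 it is 57.6% and 58.7% (noncentral t: 69.7%, 56.4% and 57.6%).

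**4. What a completers-only contrast could do.** Let p be the share of stoppers in an arm and g the amount, in SD, by which stoppers do worse than completers. The completer mean exceeds the mean of all randomised patients by p × g. With the same g in both arms, the estimate is d + g(p_combined − p_single). Neither g nor p by arm is in the documents, so the values below are assumed, with true d = 0.5:

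| Stopping, combined vs single | g = 0.3 | g = 1.0 |
|---|---|---|
| 25% vs 25% | 0.50 | 0.50 |
| 5% vs 25% | 0.44 | 0.30 |
| 25% vs 10% | 0.545 | 0.65 |

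The distortion can be nil, downward or upward.

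**5. A harsher assumed case.** There is no true difference. One arm stops according to poor T1 response (logistic, log-odds 0.5 to 2 per SD) and the other at random. The T1–T3 correlation r is 0.5 to 0.7. The bias is r × (mean T1 response of completers in the informative arm); that mean comes from integrating the logistic over a standard normal T1.

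- At 25% loss in each arm, the mean is 0.12 to 0.32 SD. The bias runs from 0.5 × 0.12 = 0.06 to 0.7 × 0.32 = 0.22 SD.
- At 40% loss in the informative arm and 10% in the other, the mean is 0.19 to 0.49 SD. The bias runs from 0.5 × 0.19 ≈ 0.10 to 0.7 × 0.49 ≈ 0.34 SD.
- With the same mechanism in both arms at 25%, the bias is zero; at 28% vs 22% it is 0.01 to 0.05 SD.

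**The case against.** Much can be said on the other side.

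- **Nominal calendar.** Four weeks of treatment plus four of follow-up put session 8 at about week 4 and T3 at about week 8, so the session labels may be shorthand. The flowchart and SPIRIT figure are not visible here and might show weeks. This softens the gap, but no visible text says that a stopper is seen at those weeks.
- **Retention rules.** The discontinuation and adherence sections say that collected data will be used. They do not say that assessment ends, and the first speaks of discontinuing treatment, not the study. A reader might infer that the protocol forbids later assessment or equates stopping with leaving. The wording does not go that far. What stands is that it schedules nothing, and that the termination criterion leans against further visits.
- **Contact provisions.** The investigator contacts participants who miss treatment or evaluation, and the retention call runs from the last intervention, not the 8th. That call could reach early stoppers, but no assessment is set for them.
- **Condensed article.** Visit windows and similar detail may be in the full protocol, and their absence is not the point. The point rests on the visit definitions and stopping rules that are printed.
- **Who is lost.** A reader might infer that the endpoint vanishes precisely in patients who stop for tolerance or response. No text links stopping to response. Other serious illness and withdrawal without a reason are also covered. The perianal pain is described as resolving after two treatments without special care, and because the combined arm also receives release, it gives no clear differential between those two arms.
- **Late completers.** A reader might also infer that made-up sessions push T2 and T3 late. Make-up sessions are not mentioned, so this is hypothetical.
- **Bias figures.** The 0.34 SD needs 10% vs 40% loss, the steepest dropout slope and r = 0.7 together. In that model stopping depends only on the observed T1, so an analysis conditioning on T1 removes the bias. The figures describe a completers-only analysis under assumption and are not a forecast for this trial.

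**Conclusion.** The point holds in limited form. Read together, the session-anchored visits, the endpoint tied to a completed course, the termination criterion and the collected-data rules leave an early stopper without a scheduled T2 or T3. The comparison on the sized endpoint is therefore restricted to completers, who may differ by arm.

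Its reach is at most about 12 to 13 of 50 per arm, if the plan's 25% dropout is right and all of it is early stopping. The size and direction of bias are unknown, because the documents give neither stopping rates by arm nor outcomes of stoppers. The claim that bias reaches two thirds of the planning effect (0.34/0.5 = 0.68) is not supported as a finding about this trial; it is the extreme of an assumed scenario. This is an inexpensive gap to close, not a defect that invalidates the design.

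**What to change.** 1. In the study design text, keep the session anchor for patients who complete eight sessions. Add that anyone who stops earlier is assessed at the nominal end of week 4 (T2) and week 8 (T3), counted from first session.
2. In the termination criteria, the discontinuation section and the adherence section, distinguish a patient who has stopped study treatment from one who has withdrawn from follow-up, and state that an incomplete course does not end assessment.
3. If a patient will not attend, collect at least NIH-CPSI by telephone, a channel the retention section already uses.

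The rules on when treatment is stopped are not touched. Moving every visit to a calendar anchor is not needed: recruitment is under way, and for completers with delayed sessions it would mix two visit definitions.

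The cost is protocol wording and a few extra visits or calls; the sample size does not change. The telephone route recovers NIH-CPSI but not sEMG, ultrasound or SSR, and nothing here recovers patients who refuse all contact. If all 50 per arm had T3, pairwise power at d = 0.5 would be about 70%, against 56 to 59% with the full 25% lost.
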